#### Performance metrics

3.5.3

The proposed methods’ accuracy, sensitivity, specificity, precision, and F1-score (Table 2) will be measured as evaluation parameters. A confusion matrix will also be extracted to provide an overview. An optimization study will be performed to determine the best hyperparameter settings. Five cross-validation will be selected, and the average values of the results will be obtained. The methods with the highest performance will be compared with the others.

**Table 2 tab2:** Calculations of performance metrics (Özcan and Alkan, 2021, 2023a, 2023b).

Accuracy	Sensitivity	Specificity	Precision	F1 score
$\frac{\mathrm{TP}+\mathrm{TN}}{\mathrm{TP}+\mathrm{TN}+\mathrm{FP}+\mathrm{FN}}$	$\frac{\mathrm{TP}}{\mathrm{TP}+\mathrm{FN}}$	$\frac{\mathrm{TN}}{\mathrm{TN}+\mathrm{FP}}$	$\frac{\mathrm{TP}}{\mathrm{TP}+\mathrm{FP}}$	$\frac{2\mathrm{TP}}{2\mathrm{TP}+\mathrm{FP}+\mathrm{FN}}$

TP: true positive; FN: false negative; FP: false positive; TN: true negative.

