#### Inclusion criteria

3.1.1

Young earthquake survivors without specific diseases who recently experienced the earthquake in our region in February 2023 will be selected. The sample sizes of 20–25 participants have been selected in similar studies (Maheu et al., 2005; Nakajima et al., 2016; Tegeler et al., 2023; Zabrecky et al., 2020). The sample size selected (*n* = 10–12 participants per group) follows the rule of thumb proposed by Julious (2005), which is widely recognized in the methodological literature as a minimum standard for pilot studies (Julious, 2005). Furthermore, our proposal will use deep learning and current artificial intelligence algorithms. Because data can be obtained from each measurement within the time-series dataset used for this purpose, a substantial amount of data can be generated through windowing and data augmentation, and transfer learning can be performed; it is assumed that a dataset from 36 participants will be sufficient. Consequently, at least 30 university students aged between 20 and 25 years who experienced and survived the earthquake will take part in the experiment. They must have experienced the earthquake as a significant and severe event. In accordance with the inclusion criteria, the participants will be healthy, non-obese men (*n* = 18) and women (*n* = 18). In particular, all participants should have experienced the earthquake disaster in the local region. All participants must be free of any chronic or acute infection, neurological, psychiatric, and/or cardiovascular disease. They must be non-smokers, have no alcohol or drug addiction, and not be under any medical treatment. Pregnant or breastfeeding women will not be included in the study.

University students who survived the earthquake in the region will be invited to volunteer for this study. The inclusion and exclusion criteria will be verified by interviewing the volunteers. Participants will then undergo a medical examination by a psychiatrist. If no problems are found, participants will be recruited for the study.

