#### Study design

3.1.2

An intervention and control group will be formed with 20 and 10 participants, respectively. The intervention and control groups will be exposed to the same mental stress.

*Control group:* 10 young healthy earthquake survivors will not receive any auditory stimulation.

Intervention group: 10 young healthy earthquake survivors will be subjected to closed-loop, real-time heart sound (PCG) stimulation to create biofeedback.Intervention group: 10 young healthy earthquake survivors will be given an auditory stimulus of their heart sound and a metronome synchronized with their mean heart rate (MHR) recorded during a calm state.

Participants will be taken individually to the experimental room and seated comfortably in a quiet and spacious environment. Before the first session, a scientific introduction, the purpose of the study, an explanation of how it will be conducted, an explanation of the mental stress to be induced, and basic information about the measurements to be taken will be provided at the information meeting (using an introduction video). The participant should feel as comfortable as possible, and no additional sources of stress should be created. Participants will be instructed to breathe normally and avoid moving their legs.

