#### Phonocardiogram data and fNIRS data

3.4.1

Heart sounds to be used as stimuli and for monitoring purposes will be converted into Mel spectrograms and input into neural networks trained with sound (OpenL3, YAMNet, and VGGish), and transfer learning will be performed.

Cognitive assessment will be performed by analyzing fNIRS signals to assess activation in specific brain regions (right, center, and left). The details are provided below. During mental stress, classification analyses will be performed between the results between the control and treatment groups and between the results of the same group before and after treatment. Then, using explainable artificial intelligence (XAI) techniques, the temporal and frequency-domain characteristics associated with these changes will be evaluated.

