#### ECG, EDR, and fNIRS data

3.4.2

The data obtained using deep learning techniques will be classified. Classification studies will be performed with deep learning to emphasize to characterize differences between the control and treatment groups, as well as differences before and after treatment within groups and to show that the difference is significant. The data will be converted into spectrogram images and processed as time-series data. A suitable pretrained network (AlexNet, SqueezeNet, GoogLeNet, etc.) will be used with transfer learning, and classification will be performed. Technical information is provided in our published articles (Özcan and Alkan, 2021, 2023a, 2023b).

On the other hand, correlation analysis will be performed using deep learning method (Alessandrini et al., 2023). Then, the features used in the classification will be evaluated using explainable artificial intelligence techniques.

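### Classification is asked to show that differences are significant, but the metrics set for it contain no test

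*Protocol article*

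**What the plan says.** Section 3.4.1 plans that "classification analyses will be performed between the results between the control and treatment groups", and also within a group before and after treatment. Section 3.4.2 states the purpose for the ECG, EDR and fNIRS data: to characterise control-treatment differences, "as well as differences before and after treatment within groups and to show that the difference is significant".

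Section 3.5.3 specifies the measurement: "The proposed methods’ accuracy, sensitivity, specificity, precision, and F1-score (Table 2) will be measured as evaluation parameters". It adds "A confusion matrix will also be extracted to provide an overview", a hyperparameter optimisation, averaging over five-fold cross-validation, and "The methods with the highest performance will be compared with the others".

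On class sizes, section 3.1.2 says "An intervention and control group will be formed with 20 and 10 participants, respectively", the 20 being two stimulation arms of 10. Table 1 gives a target of 36, and section 3.1.1 says "The sample size selected (*n* = 10–12 participants per group) follows the rule of thumb".

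The only inferential models named are in section 3.5.1: a linear mixed model or ANCOVA, in a paragraph whose primary pilot outcomes are RMSSD, HF and LF. Other measures are secondary and exploratory.

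**The concern.** The stated purpose and the stated measurement do not fit each other. Accuracy, sensitivity, specificity, precision and F1 are point descriptions of how well a classifier did on some data. Without a reference for what no effect would give, none of them can show that a difference is significant. Comparing methods with one another does not supply that reference, because all of them could be performing at the no-information level.

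Two features make the gap matter in practice. First, accuracy, precision and F1 depend on the class mix, so in an unbalanced contrast the no-information value can look respectable. Second, many networks and settings are to be tried. If the choice among them and the reported figure come from the same folds, the best figure may be optimistic.

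At stake is a statement about benefit: section 3.4 uses classification to evaluate the benefits of the biofeedback, and a claim of significance on that basis would be unsupported.

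**Working it through.** **The plan's own figure.** The classification plan contains one reproducible number, the windows per participant and measurement in section 3.5.2: 330 min × 60 s ÷ 10 s = 1980. It reproduces. No chance level, expected accuracy or power is stated for the classifiers.

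**Purpose against measurement.**
- Task (3.4.2): show that control-treatment and before-after differences are significant.
- Measurement (3.5.3): five point metrics, a confusion matrix, averages over folds, and ranking among methods.
- Tests elsewhere (3.5.1): mixed model or ANCOVA, which do not take the classification result as an outcome.

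No step connects the task to a test.

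**What a no-information rule scores.** Inputs: 20 treated and 10 control (3.1.2); 24 and 12 if the target of 36 is split equally over three arms (an assumption). Take treated as the positive class (also an assumption; the article does not name one) and a rule that always answers treated. At 20:10, TP = 20, FP = 10, TN = FN = 0. With the Table 2 formulas:
- accuracy = (20 + 0)/30 = 0.667
- sensitivity = 20/20 = 1.00
- specificity = 0/10 = 0
- precision = 20/30 = 0.667
- F1 = 2×20/(2×20 + 10 + 0) = 40/50 = 0.80
- balanced accuracy = (1.00 + 0)/2 = 0.50

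At 24:12: accuracy 24/36 = 0.667 and F1 48/60 = 0.80. At window level, with equal recording time per person, the counts are 20×1980 = 39,600 and 10×1980 = 19,800, and the values are the same.

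**How far this depends on the assumptions.**

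| Contrast and rule | Accuracy | F1 |
|---|---|---|
| Arms pooled 2:1, treated positive, always treated | 0.667 | 0.80 |
| Arms pooled 2:1, control positive, always treated | 0.667 | 0 |
| One arm against control 10:10, treated positive, always treated | 10/20 = 0.50 | 20/30 = 0.667 |

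The before-after contrast uses the same people on both sides, so the 2:1 mix does not enter. It lacks a test all the same.

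**What a real test would ask for (illustration).** Suppose one independent prediction per participant and a reference rate of 2/3. The smallest number correct that gives an exact one-sided binomial p of at most 0.05 is 25 of 30 (83.3%, p = 0.035), or 30 of 36 (83.3%, p = 0.022). An accuracy of 80% in 30 people (24 of 30) would not reach it. The planned analysis is not of this form, because it works on many windows per person.

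**The case against.** Several points on the other side are sound.

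- **The trivial rule would be visible.** Section 3.5.3 also lists specificity and a confusion matrix. Specificity 0 and an empty column expose the always-treated rule at once, and balanced accuracy is only the mean of two metrics already listed. A reader might infer that the plan would pass off 67% accuracy or F1 0.80 as a benefit. The article does not support that; it would happen only if accuracy, precision or F1 were read alone.
- **The figures are conditional.** They need pooled arms and, for F1, treated as the positive class. Pooling fits the 20 against 10 wording, but the Limitations section also compares the silent, metronome and heart-sound arms separately.
- **Selection bias is not established.** A reader might infer that the reported figure must lie above the no-effect level. Section 3.5.2 sets aside 15% for validation and another 15% for testing, and nothing says that models are chosen on test data. Optimism is possible, not shown.
- **The trial does have inference.** The HRV outcomes have the mixed model or ANCOVA, and the study calls itself preliminary. A reader might infer that the trial as a whole lacks a test; it does not.
- **Loose wording and deferral.** The article uses the word significant loosely elsewhere, and details of intervals and benchmarks commonly sit in an analysis plan.

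The last point does not remove the concern. The article itself states the inferential aim and itself fixes the metrics. That is a mismatch in the text as written, not a detail left for later.

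**Conclusion.** The point holds in this form: followed as written, the plan would claim significance for control-treatment and before-after differences from quantities that test nothing. That conclusion needs no assumption about class mix or pooling.

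The accuracy of 0.667 and F1 of 0.80 illustrate why a benchmark is needed. They apply to the pooled 2:1 contrast only, and the F1 value also needs treated as the positive class. Optimism from choosing among models may add to this if selection and reporting share folds. The HRV inference of section 3.5.1 is unaffected, so this should be corrected but does not undermine the primary analysis.

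**What to change.** **Preferred.** Delete the clause on showing significance from section 3.4.2 and call the classification descriptive. Report the Table 2 metrics beside the majority-class rate for each contrast, stating which arms are pooled and which class is positive. Leave inference to the mixed model or ANCOVA. The cost is a wording change.

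**If a test of the classification is wanted.** Use balanced accuracy or ROC AUC, folds grouped by participant, and a permutation null. For control against treatment, permute arm labels between participants, with all of a person's segments moving together. For before against after, permute the labels within participants. Repeat any selection of network and hyperparameters inside each permutation.

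Grouped folds matter here because section 3.5.2 puts off splitting by individual to future studies. With one person's windows in both training and test sets, a network can recognise the person under any relabelling. The permutation null would then sit close to the observed value and the test would have little power.

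The cost is computing time, which may be considerable when model selection is repeated, and probably less favourable figures. No new data are needed.

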#### Graphical user interface

3.5.4

Presenting a system created as project output through an interface will provide ease of use. The App Designer application will be used in MATLAB. In the user interface to be developed, the data obtained from the experimental study can be displayed in graphical and tabular forms, the desired analysis method can be selected, and the results can be displayed. Therefore, the data and results will be visualized for the study users.

## Importance of study/implications of findings

4

The ALLOSTAT0001 project, which will use the protocol described above, will analyze and investigate cardiovascular risk in young participants who have experienced trauma, such as a natural disaster or an earthquake. Neurocardiac biofeedback to preserve allostasis may be possible by applying heart sound-based stimuli. The physiological responses (electrodermal activity and neuronal activity) of these participants subjected to another type of stress (mental) will no longer be the same as before the biofeedback treatment sessions. These young participants will, therefore, learn strategies to manage new stressors in their lives and remain calm. By following them over time, using repeated measurements of cardiovascular and psychological risk markers, we can establish guidelines and recommendations for managing the health of young people at risk.

Auditory stimuli with heart rate will reduce the allostatic load by inducing resonance. Oxygenation and deoxygenation measurements in the prefrontal region of the cerebral cortex using fNIRS will provide a better understanding of cerebral activity during new stress and its attenuation generated by our method. These data can be used in neuroscience research.

The parameters collected will make it possible to improve the prediction of future cardiovascular and psychological events, not only in young people but also in adults and even children. With significant results, this protocol can be used for people who have experienced other traumas, such as natural disasters, epidemics, or war.

## Limitations

5

Although the ALLOSTAT0001 project provides a great deal of new information, it is associated with several limitations for which mitigation strategies can be proposed. The risks are detailed as follows.

Many young participants from the city where the earthquake occurred are studying in another city. This may limit our ability to recruit participants who survived the disaster, restricting the sample size to no more than 36 participants. We expect to recruit the number of participants needed to reach statistical significance in this study. For the study using deep learning techniques, 36 participants are expected to be sufficient when using transfer learning.

At the end of the project, missing data may occur. When collecting signals, we may notice that the signal is incomplete or has anomalies. As missing data can limit statistical comparisons between groups, we will reduce this problem by recruiting other participants. We will recruit an additional 10 participants who will provide backup data. If we cannot recruit participants aged 20–25 years because many students were absent (at the end of their school holidays) during the earthquake in 2023, we can extend the age range to 18–25 years. In addition, we will take the necessary steps in the statistical analysis plan to address the missing data.

Each participant will be invited to return 4 weeks after the final session for a follow-up evaluation. However, the start of holiday period may make it challenging to collect data after the event. We will take care to plan the sessions and the day of the follow-up evaluation, prioritizing participants who will be staying in the city during the holiday period.

This study is a preliminary investigation aimed at exploring whether real time, closed-loop phonocardiogram stimulation enables individuals to manage acute stress more effectively and whether the effects of this treatment persist for up to 4 weeks. The design of a further, longer-term, and more comprehensive study will help to substantiate claims regarding long-term cardiovascular or psychological outcomes.

This study did not include an acoustically equivalent sham arm (scrambled sound), thus limiting the ability to completely isolate the specific effects of real-time heart sounds from the non-specific effects of listening and directed attention. However, the comparison between the silent, metronome, and heart-sound arms provided a partial separation of these effects. The main objective of this study is to explore the overall efficacy of the intervention under real-world conditions rather than to isolate its precise mechanism of action. Future studies incorporating an acoustically matched sham arm are necessary to confirm the specificity of the proposed mechanism.

Another limitation is that the first session, the subsequent 10 sessions, and the day of the follow-up evaluation for all groups may not be conducted in the same season. As seasons are known to affect physiological parameters (Goswami et al., 2021; Goswami et al., 2020; Trozic et al., 2020), we will endeavor to conduct most recordings during a single season. This should prevent differences in ECG signals owing to seasonal changes.

Because of the front-end morphology of each participant, during measurements with fNIRS, not all 16 channels can produce significant signals. We will, therefore, use the maximum number of active channels for all participants. We will use a headband or cap to improve contact with the prefrontal area for all participants. At worst, 12 channels will provide sufficient information about the right, central, and left prefrontal cortex activity.

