## Methods/design

3

The Project has received ethics approval from Harran University with the decision of the clinical research ethics committee. The study was registered under the number E-76244175-050.04-346993, on the 10th of June 2024. The study will be conducted at Kahramanmaras Sütçü İmam University in Türkiye. The study was subsequently registered with www.ClinicalTrials.gov under the registration number NCT06919055 in March 2025 and follows the Standard Protocol Items: Recommendations for Interventional Trials (SPIRIT) reporting guidelines (Chan et al., 2013). All items from the World Health Organization Trial Registration Data Set are summarized in Table 1 according to the SPIRIT reporting guidelines. Data collection began in December 2024 and completed by 30 June 2025.

**Table 1 tab1:** Items from the World Health Organization trial registration dataset.

Section/item	Information
Primary Registry and Trial Identifying Number	ClinicalTrials.gov, NCT06919055
Date of registration in primary registry	17 March, 2025.
Secondary identifying numbers	124S102
Source(s) of monetary or material support	The Scientific and Technological Research Council of Türkiye (TÜBİTAK)
Primary Sponsor	[name] and [name]
Secondary sponsor (s)	[name], [name]
Contact for public queries	[name], [contact]
Contact for scientific queries	[name], [contact] and [name] [contact]
Public title	Allostat0001
Scientific title	Biofeedback with Heart Sound Following Trauma
Countries of recruitment	Turkey
Health condition(s) or problem(s) studied	This study aims to examine how individuals cope with trauma-related situations using a biofeedback method, which could be developed to manage stress-related coping.
Intervention(s)	1. Control 2. Heart sound stimulation 3. Metronome with ECG rate stimulation
Key inclusion and exclusion criteria	36 earthquake survivor university students aged between 20 and 25 years will participate in the experiment. Participants will be healthy, non-obese men (*n* = 18) and women (*n* = 18). In particular, all participants should have experienced an earthquake disaster in the local region. All participants should be free of any chronic or acute infection, neurological, psychiatric, and/or cardiovascular disease. They must be non-smokers, have no alcohol or drug addiction, and not be under any medical treatment. Pregnant or breastfeeding women will not be included in the study.

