#### Statistical methods

3.5.1

RMSSD, HF, and LF derived from HRV will be the primary pilot outcomes for estimating the effect size and variance, with a view to calculating the sample size for a future confirmatory trial. The primary outcomes will be assessed at the final session and compared with those obtained at the first session. The analyses will be conducted using a linear mixed-model (LMM), with group and time as fixed effects or using an analysis of covariance (ANCOVA). Other measures, such as electrodermal activity, respiratory rate, and neuroimaging, will be treated as secondary endpoints for exploratory purposes.

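### The plan expects enough participants to reach statistical significance, but derives no such number; separately, its stated sample sizes conflict, and its effect-size estimate is too imprecise to size the next trial unadjusted.

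*Protocol article*

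**What the plan says.** **Expectation.** Section 5 (Limitations) states: "We expect to recruit the number of participants needed to reach statistical significance in this study". The same section calls the study a preliminary investigation.

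**Purpose.** Section 3.5.1 (Statistical methods) says that "RMSSD, HF, and LF derived from HRV will be the primary pilot outcomes for estimating the effect size and variance", and continues "with a view to calculating the sample size for a future confirmatory trial". The analysis is a linear mixed model or ANCOVA comparing the final session with the first.

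**Basis of the size.** Section 3.1.1 gives three reasons: similar studies with 20–25 participants, a pilot rule of thumb of 10–12 per group, and the amount of windowed and augmented data available for deep learning.

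**The size itself.**
- Table 1 (section 3): "36 earthquake survivor university students aged between 20 and 25 years will participate in the experiment", made up of 18 men and 18 women, with a target of 36.
- Section 3.1.1: "at least 30 university students aged between 20 and 25 years who experienced and survived the earthquake", and in the same paragraph 36 participants and again 18 men and 18 women.
- Section 3.1.2: "An intervention and control group will be formed with 20 and 10 participants, respectively", with the 20 split into two arms of 10.
- Section 5: a ceiling of 36, followed by a further 10 participants recruited as backup.

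**The concern.** A statement that recruitment will reach the number needed for significance implies a sample size calculation against a target effect. The article contains none, and the rationale it does give is that of a pilot. A reader who takes the sentence at face value may give a non-significant or a significant result more weight than arms of 10–12 can bear. Section 4 encourages the second error, since it makes extending the method to other traumas depend on significant results.

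Two further matters need separating from this. The sizes do not agree with each other, so the planned number per arm cannot be read off the document. And one of the two quantities that section 3.5.1 wants from the pilot, the effect size, is estimated much less well than the other, the variance.

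**Working it through.** **1. Can the stated size be reproduced?** Only as rule-of-thumb arithmetic: 3 × 10 = 30 and 3 × 12 = 36. The article gives no alpha, power, effect size or SD for a power calculation. The inputs below are therefore assumptions: two-sided alpha 0.05, power 0.80, standardised difference d and, where used, baseline correlation r.

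**2. Detectable difference.** For two arms of sizes n1 and n2, t-test power uses the noncentral t with n1 + n2 − 2 degrees of freedom and noncentrality d / √(1/n1 + 1/n2). Baseline adjustment (ANCOVA) multiplies the detectable d by √(1 − r²).

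| Comparison | Detectable d, 80% power |
|---|---|
| 10 vs 10 | 1.32 |
| 12 vs 12 | 1.20 |
| Both intervention arms vs control, 20 vs 10 | 1.12 |
| Both intervention arms vs control, 24 vs 12 | 1.02 |
| 10 vs 10, r = 0.6 (factor 0.8) | 1.06 |
| 12 vs 12, r = 0.6 (factor 0.8) | 0.96 |
| 10 vs 10, r = 0.7 | 0.95 |
| 12 vs 12, r = 0.7 | 0.86 |

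**3. Pairwise power over a range of true effects, without baseline adjustment.**

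| True d | 10 per arm | 12 per arm |
|---|---|---|
| 0.3 | 9% | 10% |
| 0.5 | 18% | 22% |
| 0.8 | 40% | 47% |
| 1.0 | 56% | 65% |
| 1.2 | 72% | 80% |

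With r = 0.7, power at d = 0.5 rises to 32% and 38%, and at d = 0.8 to 66% and 75%. By the normal approximation, n per arm = 2(1.96 + 0.84)²/d² = 15.7/d², so d = 0.5 needs 63 per arm and d = 0.8 needs 25.

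**4. Do the sizes agree?** The 10–12 per group, the minimum of 30 and the maximum of 36 fit together as a range of 30–36. Two things do not fit:
- Section 3.1.2 fixes 10 + 10 + 10 = 30. Table 1 and section 3.1.1 fix 18 + 18 = 36.
- Section 5 sets a ceiling of 36, then adds 10: 30 + 10 = 40 or 36 + 10 = 46, both above the ceiling.

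**5. How well does the pilot estimate the variance?** The 95% limits for an SD pooled over three arms are √(df/χ²) times the estimate:
- 30 people, df = 27: √(27/43.19) = 0.79 to √(27/14.57) = 1.36.
- 36 people, df = 33: √(33/50.73) = 0.81 to √(33/19.05) = 1.32.

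**6. How well does it estimate the effect size?** SE(d) = √(2/n + d²/(4n)). For an observed d = 0.5:
- n = 10: √(0.2 + 0.00625) = 0.454; 0.5 ± 1.96 × 0.454 = −0.39 to 1.39.
- n = 12: √(0.1667 + 0.0052) = 0.415; 0.5 ± 1.96 × 0.415 = −0.31 to 1.31.

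At the upper limits the next trial would need 15.7/1.39² = 8.1, so 9 per arm, or 15.7/1.31² = 9.1, so 10 per arm. Both lower limits are below zero, so no finite size follows from them.

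**The case against.** Several points on the other side stand.

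- **The pilot size is legitimate.** A rule of thumb of 10–12 per group is a recognised basis for a pilot, and step 5 shows that it serves the variance aim reasonably well. A reader might infer that the study can deliver neither of its aims; the document's own design does not support that.
- **The size conflict does not cause the low power.** At d = 0.5, 10 and 12 per arm give 18% and 22%. Settling on either number would leave the significance sentence just as unsupported.
- **Mis-sizing of the next trial is not a stated plan.** A reader might infer that the confirmatory trial will be badly under- or over-sized. Section 3.5.1 does not say that the observed effect will be used unadjusted, or that only significant results will be carried forward. The imprecision matters only if the estimate is used that way.
- **Misreading of the result is not certain.** The words on pilot outcomes, preliminary investigation and a future confirmatory trial point towards caution, although section 4 pulls the other way.
- **The power figures rest on assumptions.** With a difference of about 1.2–1.3 SD, or about 0.9 SD with a strongly correlated baseline, the arms would suffice. The article does not claim such an effect.

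None of this supplies a basis for the significance sentence or removes the conflict between section 3.1.2 and Table 1.

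**Conclusion.** The point holds in three separate parts.

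1. The expectation of reaching significance is unsupported as written, and the article's own pilot rationale contradicts it. Under the assumed two-sided 5% test, only differences of roughly 1.0–1.3 SD have 80% power without baseline adjustment, whichever size and grouping of arms is taken. This goes beyond what an analysis plan could settle, because the article makes a positive claim.
2. The planned size is contradictory: 30 in exact arms of 10, against 36 in exact halves by sex, with a ceiling of 36 that the 10 backups would exceed.
3. For the next trial, the variance estimate is usable with allowance for its uncertainty. The effect-size estimate is too imprecise to be used unadjusted. This part is conditional on how the estimate would be used, which the article leaves open.

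The documents do not support treating the pilot as too small for its purpose, or the conflict in sizes as the reason for low power.

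**What to change.** - Delete the significance sentence from section 5.
- State one size per arm and one total, the same in Table 1 and sections 3.1.1, 3.1.2, 3.5.2 and 5, and reconcile the 10 backups with the ceiling of 36.
- Say that differences between arms will be reported as estimates with 95% intervals.
- In section 3.5.1, say that the next trial will take from this pilot the variance, allowing for its uncertainty, and the session-to-session correlation. Its target difference will come from a minimum important difference stated in advance, not from the effect observed here. How to allow for uncertainty in the SD is open; an upper confidence limit is one accepted choice.

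The cost is wording only. Section 3 gives data collection as completed by 30 June 2025, so nothing here asks for more participants. The price is that the stated expectations become less favourable.
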